### 9.2 EXPECTED ADVERSE EVENTS

The following negative treatment-related events are considered expected in the proposed trial given previous research on ICBT for depression (61) and other disorders (62):

- Increased depressive symptoms
- Thoughts of death and suicide
- Increased stress due to tempo and workload
- Feeling worse while processing treatment content
- Increased irritability
- Increased anxiety/stress
- Increased tiredness/fatigue
- Increased/decreased sleep
- Headaches
- Not having confidence in the treatment
- Not feeling that the treatment produces any results
- Feeling that the treatment is not always motivating
- Not always understanding the treatment

It is important to note that adverse events may also be symptoms of the underlying condition, rather than the intervention itself. Adverse events will be closely monitored by the therapist and reported in accordance to the procedures outlined in this protocol.

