## **5 PROJECT DESCRIPTION**

### **5.1 DESIGN**

This will be a single site randomised controlled trial with national recruitment that will include 215 adolescents with mild to moderate depression. Participants will be randomised to receive 10 weeks of either (1) guided I-BA or (2) self-guided I-BA or (3) treatment as usual (TAU), at a ratio of 1:1:1 (72 in each group). TAU will be provided by regular mental health care clinics, within either primary or secondary care.

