## **6.4 TREATMENT**

### **6.4.1 GUIDED AND SELF-GUIDED I-BA**

The intervention arms consist of internet-delivered BA with (guided) and without therapist-support (self-guided) and involve both the adolescent and their caregiver. The adolescent and the caregiver are provided with their own separate programs and login to the platform.

Each of the I-BA interventions consists of 8 modules, delivered over a maximum of 10 weeks. In certain circumstances (e.g., illness or holidays), participants in guided ICBT can pause their therapist-support for one or two weeks. After 10 weeks, all modules will be made available for the participant (regardless of how many modules s/he has completed). The adolescent and caregiver can continue to access all treatment modules for the whole follow-up period (3 months), but without therapist-support.

During guided I-BA, participants have regular contact with a trained therapist inside the platform. The therapist provides feedback, answer questions, and reminds you to complete the next module if required. Communication is possible via traditional text messages (resembling e-mail) or via comments on specific worksheets. When the participant receives a message on the platform, s/he also gets an SMS reminder to her/his phone. The therapist usually logs in daily (on workdays; at minimum every 48 hours). Therapist time is automatically logged in to the platform. Participants are typically in contact with their therapist several times a week. Phone calls are possible if the participant/therapist for a certain reason feels it is needed but are generally kept to a minimum. The participants are welcome to contact their therapist at any time, who will reply during office hours.

An overview of the treatment is presented in **Table 1**. The treatment manual, developed by [name], consists of evidence-based interventions adapted to an online format inspired by previously published treatment manuals on behavioral activation for adolescents (36, 53). The main goal of the BA is to increase engagement in values-based activities and decrease avoidant behaviors that serve to maintain depression. The adolescent will learn about depression, how behavioral activations works, monitor their own activities, plan and do more values-based activities and deal with obstacles to getting in touch with positive reinforcement, such as avoidance behaviors.

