The adolescents will also learn about common sleep problems in depression and how they can improve their sleep. Sleep disturbances commonly co-occur with depression in adolescents (54). However, research on this area is lagging behind and the Board of Health and Welfare provides no guidelines for treatment of insomnia when co-occurring with depression (55). The British National Institute for Health and Care Excellence's (NICE) guidelines for treatment of depression states that patients with sleep problems in depression should be offered advice on sleep hygiene (56). Therefore, we decided to include brief psychoeducation on sleep problems and advice on adaptive sleep behaviors (e.g., keeping regular sleep hours) early in treatment, to enable continuous work with establishing better sleep routines during the rest of the treatment.

The self-guided I-BA is identical to the guided I-BA intervention, however without therapist support. To ensure patient-safety, there will be clear instructions to the patients and primary caregivers how to get in contact with the study team in case of acute problems, and there will be clinical routines to detect and manage deterioration or suicidal tendencies.

We included a caregiver program in I-BA because caregivers are a significant part of the adolescents' daily life and can provide support with treatment assignments. Caregivers may also be part of an ineffective communication pattern that contributes to maintained depression. Involving caregivers facilitates modification of these unhelpful patterns. Caregivers are also commonly engaged in other BA-protocols for adolescents (53, 57). The caregiver program is consistent with principles from Parent Management Training (PMT; (58, 59), that teach caregivers positive parenting skills, aiming at strengthening the relationship between caregivers and their children.

The caregiver program consists of 8 modules, including psychoeducation about depression, how to support their adolescent suffering from depression, reviews of the content in the adolescent program, caregiver coping strategies, collaborative problem-solving and effective communication skills. Both the adolescent and the caregiver in guided I-BA have individual access to the same therapist. See **Table 1** below for more details on the treatment content.

**Table 1.** Treatment overview of I-BA

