#### **6.4.3 THERAPIST TRAINING, SUPERVISION AND MONITORING**

All therapists will receive training before the trial starts. They will be introduced to the use of the platform and the I-BA protocol during a one-day training by the treatment constructor ([name]). Regular supervision will be held to discuss treatment progress for individual patients and follow up on clinical needs and potential adverse events. Protocol violations will be recorded.

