#### **9.4 HANDLING OF ADVERSE EVENTS**

Adverse events will be noted by the trial coordinator in a specific log (including date, recorded clinical symptoms, and a brief description of the event). The research team could be notified about adverse events in numerous ways, including through direct (text or telephone) communication with the participant, or at follow-up assessments. Regular meetings (treatment conferences) will be held within the research team where treatment progress and potential adverse events are discussed. Cut-off scores on the suicidal item in QIDS-A17 (self-rated depressive symptoms), might also be indicators of adverse events, and thus be registered in the AE-log. Scores of 2 or 3 points on the suicide item corresponding to a yes to “I think of suicide or death several times a week for several minutes” or “I think of suicide or death several times a day in some detail, or I have made specific plans for suicide or have actually tried to take my life”, will automatically raise a flag in the BASS system, to directly notify members of the research team to follow this up (via the telephone) with the participant.

SAEs will be recorded in the patient’s medical record (Take Care), as well as in the trial coordinator’s log. Appropriate action will be taken in the case of SAE, making sure the participant will get in contact with suitable health care services. Events will be considered as potentially treatment-related up to the 3-month follow-up, where the reporting of adverse events will terminate. The PI will immediately notify the Sponsor of any events of SAE. The PI and sponsor will work together to identify the extent of the SAE and to determine what urgent safety measures are required.

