Adverse events will be carefully monitored in all three groups throughout the trial. Where necessary, the participant's local teams or GP will be informed about the event. The TAU arm means contact with regular health care which will ensure patient safety.

Participants may worry about computer safety and confidentiality. To prevent this, families will receive information about the risks and precautions that are being taken when using communication technology (e.g., encrypted server technology and double authentication with password and SMS-code).

Each participant will be assigned a unique trial identification number at the point of randomisation. This number will be recorded on all paper datasheets and in the electronic trial database. A hard copy of a record sheet linking patient identity, contact details, screening number, and trial identification number for all participants will be kept securely in a locked filing cabinet separate from datasheets. This will also be stored in a password protected electronic database, which only will be accessible to authorized users. All data will be kept secure at all times and maintained in accordance with the requirements of GCP regulations. ELN will be used to log all significant decisions during the trial.

In conclusion, the risks for the participants are considered to be limited and temporary. The risks will be far outweighed by the potential benefits for the participant and the scientific value of the study.

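### Adverse event ascertainment is not standardised across the three arms, so by-arm counts from the log are at risk of detection bias; separately, two sections disagree on when recording ends

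*Protocol*

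**What the plan says.** On who detects adverse events, section 9.2 reads: "Adverse events will be closely monitored by the therapist and reported in accordance to the procedures outlined in this protocol". It names no arm. Section 6.4.3 adds a second route through the therapists: "Regular supervision will be held to discuss treatment progress for individual patients and follow up on clinical needs and potential adverse events".

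On who has a therapist, section 6.4.1 says of guided I-BA: "Participants are typically in contact with their therapist several times a week". Of the other internet arm it says: "The self-guided I-BA is identical to the guided I-BA intervention, however without therapist support". Section 5.1 places the control arm outside the study team: "TAU will be provided by regular mental health care clinics, within either primary or secondary care".

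On the general routes, section 9.4 gives an open list: "The research team could be notified about adverse events in numerous ways, including through direct (text or telephone) communication with the participant, or at follow-up" (the last item being the assessment visits). It also mentions team conferences. A score of 2 or 3 on the QIDS-A17 suicide item raises an automatic flag and a telephone call, but entry of that score in the log is worded as a possibility and not as a rule.

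On the end of recording, section 9.4 treats events as potentially treatment-related "up to the 3-month follow-up, where the reporting of adverse events will terminate". Section 12 says: "Adverse events will be carefully monitored in all three groups throughout the trial". Sections 6.3 and 6.6 end the trial at the last participant's 12-month follow-up.

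**The concern.** An adverse event count is comparable between arms only if an event has the same chance of being recorded in each. Here the person named as monitor exists in one arm of three, and that arm also has by far the most frequent contact with study staff. An adolescent who mentions headaches, fatigue or feeling worse to a guided therapist can enter the log that week. The same complaint in self-guided I-BA or TAU depends on the family contacting the team or raising it at an assessment.

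Section 3 asks whether internet treatment could be entirely self-guided without loss of efficacy or safety. Lower detection in the self-guided arm would push the log towards a reassuring answer to that question. No later analysis can recover events that were asked about unequally.

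The disagreement on when recording ends is a different defect. It leaves unclear whether an event disclosed after the 3-month follow-up belongs in the log.

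**Working it through.** The protocol states no adverse event rate, detection rate or safety sample size, so there is no figure to reproduce. The check is mainly a comparison of text.

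**1. Which route reaches which arm**

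| Route (section) | Guided | Self-guided | TAU |
|---|---|---|---|
| Therapist monitoring (9.2) | Yes | No therapist | No study therapist |
| Therapist supervision (6.4.3) | Yes | No | No |
| Messages and calls (9.4) | Possible, on top of regular therapist contact | Possible; instructions for acute problems (6.4.1) | Possible |
| Team conferences (9.4, 12) | Yes | Not excluded | Not excluded |
| Reports at assessments (9.4) | Yes, no fixed question | Same | Same |
| Weekly QIDS-A17 suicide flag (9.4, 12) | Yes | Yes | Yes |
| NEQ-20 at post-treatment and 3 months (Table 2) | Yes | Yes | Yes |

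The first two rows operate in guided I-BA alone. Section 5.7.3 confirms that there is no therapist in the self-guided arm: its adherence scale drops the item on communication with the therapist, and a research assistant does the rating.

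**2. What the shared routes cover**

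The automatic flag concerns one of the 13 expected events listed in section 9.2, thoughts of death and suicide. NEQ-20 is broader, but section 9.4 does not feed it into the log, and the version history for 1.1 says it is reported separately. Table 2 has no row for an AE or SAE question. Non-suicidal events therefore enter the log through the routes that are unequal or unstructured.

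**3. Illustration of size (assumed inputs)**

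Let p be the true proportion with an event, equal in all arms, and s the share detected. The log shows p·s. The apparent ratio is s(guided)/s(other), whatever p is, and the apparent difference is p·[s(guided) − s(other)]. I assume s = 90% in guided I-BA and take n = 72 per arm from section 5.1. The chance of a false signal against guided I-BA at two-sided 0.05 is Φ[(difference − 1.96·SE₀)/SE₁], with SE₀ pooled and SE₁ unpooled.

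Example with p = 30% and 60% detected elsewhere: 0.30 × 0.90 = 0.27; 0.30 × 0.60 = 0.18; difference 0.09; ratio 1.5. SE₀ = √(2 × 0.225 × 0.775/72) = 0.0696. SE₁ = √((0.27 × 0.73 + 0.18 × 0.82)/72) = 0.0692. Φ[(0.09 − 0.1364)/0.0692] = Φ(−0.67) = 25%.

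| Detection elsewhere | Ratio | Difference at p = 20%, 30%, 50% | False signal |
|---|---|---|---|
| 90% | 1.0 | 0, 0, 0 points | 2.5% |
| 75% | 1.2 | 3.0, 4.5, 7.5 points | 7%, 9%, 15% |
| 60% | 1.5 | 6, 9, 15 points | 17%, 25%, 46% |

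**4. The two end points for recording**

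From section 6.5.3, with 4.348 weeks per month, and reading the TAU clock as 11 weeks from referral before the follow-up months begin:

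- To the 3-month follow-up: 10 + 3 × 4.348 = 23.0 weeks (I-BA); 11 + 13.0 = 24.0 weeks (TAU).
- To the 12-month follow-up: 10 + 12 × 4.348 = 62.2 weeks (I-BA); 63.2 weeks (TAU).
- Disputed part: 9 × 4.348 = 39.1 weeks, which is 63% (I-BA) or 62% (TAU) of the time to 12 months.

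The disputed period is the same nine months in every arm.

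**The case against.** There is a good case on the other side. The protocol does not rank its routes, so nothing shows that the log is fed mainly by therapists. Every arm attends the assessments at which events may be reported. Conferences are not limited to guided patients, and section 6.4.1 promises routines for detecting deterioration in the self-guided arm. NEQ-20 goes to adolescent and caregiver alike and ends with an open question on other negative events. Leaving room for judgement before logging a suicide-item score is defensible, because section 9.2 notes that events may be symptoms of the depression itself, and that latitude is the same in all arms. Section 8 states no between-arm test of adverse events, and safety is not among the objectives in section 4.

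Much of this stands and limits the point. A reader might infer that the safety comparison is biased as a matter of fact, or that self-guided participants go unmonitored. The documents support neither. No detection rates are given, no formal comparison is specified, and suicidality is monitored weekly in the same way in all three arms.

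The objection does not remove the asymmetry in the first two rows of the table, or the absence of a fixed question. Section 12 promises monitoring in all three groups, and any by-arm listing of the log will be read as a comparison, tested or not.

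On the end date, one can argue that section 9.4 ends reporting while section 12 speaks only of monitoring. The protocol does not draw that distinction. Section 9.4 also gives no end date for notifying the sponsor of SAEs, so the status of a late SAE remains open.

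**Conclusion.** The point holds as a risk. Ascertainment is not standardised across arms, and for non-suicidal events the log will tend to detect more in guided I-BA. The direction follows from the text: guided I-BA looks less safe, and self-guided I-BA and TAU look safer. The size does not follow from the text. The ratios of 1.2 and 1.5 and the false-signal chances of 7% to 46% rest on assumed detection rates and equal true rates, and show only what modest inequality could do with 72 per arm.

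The conflict between sections 9.4 and 12 is a separate drafting defect. A reader might infer that it adds to the bias between arms. It does not, because either end point applies to all arms alike. It leaves about nine months per participant with undefined recording status.

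**What to change.** - Ask one standard AE/SAE question of all participants at the post-treatment and 3-month assessments and enter the answers in the log. Placing it with the online questionnaires, or after the CDRS-R has been rated, avoids added strain on assessor blinding.
- State one rule, the same in every arm, for when a QIDS-A17 suicide-item flag is recorded in the log.
- Base any between-arm safety comparison on these sources and NEQ-20. List therapist-detected and spontaneously reported events separately, with a note that their detection differs by arm.
- Reword section 9.2 so that it describes monitoring in all three arms.
- Separately, reconcile section 9.4 with section 12 on when recording ends, and say whether the stop at 3 months applies to SAEs.

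The cost is one short question at each of two existing assessments, plus wording in sections 9.2, 9.4 and 12 and a row in Table 2. QIDS-A17 and NEQ-20 are already collected. For participants already past those assessments the question cannot be asked on time, so a full-sample comparison would have to rest on QIDS-A17 flags and NEQ-20.

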### **9.3 ASSESSMENT OF ADVERSE EVENTS**

#### **A. ASSESSMENT OF CAUSAL RELATIONSHIP**

The assessment of the relationship between adverse events and the administration of the treatment is a decision based on all available information. The final decision is taken by the PI, or if she is not present team member and medical doctor [name]. If the event is a result of the administration of any of the research procedures, then it will be classed as related.

All AE will be categorized either as likely related, possibly related, or not related, in accordance with the definitions below:

**Likely related:** Clinical event occurring within a reasonable time after administration of the intervention. It is unlikely that the event can be attributed to underlying disease or medications, but is most likely caused by the intervention.

**Possibly related:** Clinical event occurring within a reasonable time after administration of the intervention. The event could be explained by the intervention, but there is insufficient information to determine the relationship. The event could be explained by an underlying disease or medications.

**Not related:** Clinical event that is not reasonably related to the intervention. The event is unlikely related to the intervention and can be explained by medications or underlying disease.

#### **B. ASSESSMENT OF INTENSITY**

In addition to assessing the causal relationship between administration of the intervention and AE, an assessment of the intensity of the event is required. The following classifications will be used:

**Mild:** The adverse event is mild and transient in nature and does not affect the subject's normal life, and does not require any intervention or treatment (e.g., temporary insomnia, mild headache).

**Moderate:** The adverse event causes deterioration of function but does not affect health. The event can be sufficiently unpleasant and interferes with normal activities but does not completely obstruct them. May require interventional treatment (e.g., fever requiring antipyretic medication).

**Severe** – event results in significant symptoms that prevents normal daily activities; may require hospitalization or invasive intervention (e.g., anemia resulting in blood transfusion).

#### **C. ASSESSMENT OF SERIOUSNESS**

The investigator is responsible for assessing the seriousness (**serious** or **non-serious**). If the incident is considered serious, this should be reported as a serious adverse event (SAE) by the investigator to the sponsor.

#### **9.4 HANDLING OF ADVERSE EVENTS**

Adverse events will be noted by the trial coordinator in a specific log (including date, recorded clinical symptoms, and a brief description of the event). The research team could be notified about adverse events in numerous ways, including through direct (text or telephone) communication with the participant, or at follow-up assessments. Regular meetings (treatment conferences) will be held within the research team where treatment progress and potential adverse events are discussed. Cut-off scores on the suicidal item in QIDS-A17 (self-rated depressive symptoms), might also be indicators of adverse events, and thus be registered in the AE-log. Scores of 2 or 3 points on the suicide item corresponding to a yes to “I think of suicide or death several times a week for several minutes” or “I think of suicide or death several times a day in some detail, or I have made specific plans for suicide or have actually tried to take my life”, will automatically raise a flag in the BASS system, to directly notify members of the research team to follow this up (via the telephone) with the participant.

SAEs will be recorded in the patient’s medical record (Take Care), as well as in the trial coordinator’s log. Appropriate action will be taken in the case of SAE, making sure the participant will get in contact with suitable health care services. Events will be considered as potentially treatment-related up to the 3-month follow-up, where the reporting of adverse events will terminate. The PI will immediately notify the Sponsor of any events of SAE. The PI and sponsor will work together to identify the extent of the SAE and to determine what urgent safety measures are required.

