#### ***Internet Intervention Patient Adherence Scale (iiPAS)***

The iiPAS is a clinician-rated measure of patient adherence to internet-delivered behavioral interventions (39) with 5 items rated on a 0 to 4 Likert scale with total score ranging from 0 to 20, where 0 indicates no adherence and 20 perfect adherences. The scale covers client's work pace, engagement, communication with the therapist, motivation for change, and login frequency. The iiPAS has demonstrated excellent internal consistency and good construct validity as well as a strong association with objective measures of patient activity in ICBT(39). For participants in the self-guided group, we will use an adapted version excluding item 3 since communication with therapist is not applicable, and a research assistant will make the rating at post-treatment.

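### Section 9.4 ties the automatic suicide-risk flag to the adolescent's own form and states no alert for the same item on the caregiver's week-5 form

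*Protocol*

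**What the plan says.** Section 9.4 specifies the alert in detail: a score of 2 or 3 on the suicide item of the QIDS-A17 "will automatically raise a flag in the BASS system, to directly notify members of the research team to follow this up (via the telephone". It describes the QIDS-A17 as a self-rating and reproduces the two triggering responses in the first person. The other routes it names are direct contact with the participant, follow-up assessments and team meetings. None of these is automatic.

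The adolescent completes the QIDS-A17 weekly, within a 7-day window, to monitor depressive symptoms and suicidality (section 6.5.1). Section 12 relies on these weekly ratings in all arms.

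The caregiver completes a parallel version, the QIDS-A17-PR, with the same questions reworded to describe the adolescent (section 5.7.5). Both versions are entered directly into BASS (section 5.7). Table 2 schedules the caregiver version at baseline, after 5 weeks, post-treatment and at the 3- and 12-month follow-ups.

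Section 9.2 lists "Thoughts of death and suicide" among the expected events. Section 12 promises: "Adverse events will be carefully monitored in all three groups throughout the trial". For the self-guided arm, section 6.4.1 says that "there will be clinical routines to detect and manage deterioration or suicidal tendencies", and that patients and caregivers will be told how to reach the study team in acute situations.

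**The concern.** The caregiver form is a second source on suicidal thinking that does not depend on what the adolescent chooses to disclose. The trial already collects it, in the system that raises the flag, yet the one rule that turns an answer into a telephone call is written for the adolescent's form alone.

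The case that matters is disagreement or absence. A caregiver reports frequent suicidal thoughts or plans, while the adolescent scores 0 or 1 that week or submits nothing. The trial would then hold a caregiver's report of risk with no stated duty on anyone to act on it. For a trial of adolescents with depression that lists suicidal thoughts as an expected event, that is worth closing.

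**Working it through.** No statistical figure is at issue. The check sets the sections side by side and counts the forms concerned.

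1. **Trigger.** Section 9.4: a score of 2 or 3 on the suicide item of the self-rated QIDS-A17. The first-person wording of the two responses fits only the adolescent's form.
2. **Does the caregiver form carry the item?** Section 5.7.5 says that the caregiver answers the same questions. Section 9.4 treats the suicide item as part of the QIDS-A17. So the caregiver form includes it.
3. **Is it in the system that raises the flag?** Section 5.7: yes, caregiver-reported measures go directly into BASS.
4. **When does it stand alone?** Table 2 places the clinician-rated CDRS-R, CGI-S and CGAS at baseline, post-treatment, 3 months and 12 months. At those four points a clinician also assesses the adolescent. The remaining caregiver time point, after 5 weeks, has no clinician-rated measure.
5. **What happens at week 5, as written:**

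| Adolescent suicide item | Caregiver suicide item | Stated automatic alert |
|---|---|---|
| 2 or 3 | any | Yes |
| 0 or 1 | 2 or 3 | None |
| Form not submitted | 2 or 3 | None |

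Section 5.6 allows no missing single items. An unanswered suicide item therefore means that the whole form is missing.

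6. **How many forms.** One week-5 caregiver form per participant: 1 × 215 = 215 at most, or 215 / 3 = about 72 per arm. This bounds the forms, not the reports of risk.
7. **What comes next.** Adolescent weekly forms left after week 5: 10 − 5 = 5, the first about 7 days later. The next clinician assessment comes 10 − 5 = 5 weeks later if held as treatment ends. At the 2-month limit in section 6.5.2 (about 61 / 7 = 8.7 weeks) it comes about 5 + 8.7 = 13.7 weeks later. These are intervals in the schedule. They are not estimates of time that a risk goes undetected, because the weekly forms and the other routes continue.

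**The case against.** **The flag may already cover the caregiver form.** Table 2 labels both versions QIDS-A17, and nothing says that the flag is off for the caregiver. It may be set in practice. What remains is that the only written rule points to the adolescent's form, and BASS would be configured and audited from that rule.

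**A caregiver who knows of suicidal plans would call.** At least one caregiver must take part (section 5.5.1), and section 6.4.1 promises contact instructions. Weekly conferences with a psychiatrist present (section 12) may also bring the answer to light. This stands, and it makes the harmful case less likely. It does not make the written rule cover that case.

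**A stronger reading is tempting.** Section 9.2 says "Adverse events will be closely monitored by the therapist and reported in accordance to the procedures outlined in this protocol", whereas section 6.4.1 says "The self-guided I-BA is identical to the guided I-BA intervention, however without therapist support", and section 5.7.3 adapts the adherence scale because "communication with therapist is not applicable". For the control arm, section 12 offers another safeguard: "The TAU arm means contact with regular health care which will ensure patient safety". A reader might infer that a self-guided adolescent who stops submitting weekly forms has nobody to notice. The documents do not support that:

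- Section 9.4 does not depend on a therapist. The trial coordinator keeps the log, the flag goes to the research team, and cases are discussed in team meetings. The sentence in 9.2 is loosely worded and does not set the operating arrangement.
- Section 6.4.1 promises detection routines in its paragraph on the self-guided arm. They are not described, but an undescribed routine is not an absent one, and such steps may sit in clinic procedures not shown here.
- A single missed form is largely covered by the next one, about 7 days later. The protocol gives no rate of missed weekly forms, so the extent of longer silences is unknown.

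What is left on lapsed forms is missing operating detail.

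**Conclusion.** The point holds in a narrow form. As written, section 9.4 states no alert for a caregiver score of 2 or 3 on the suicide item at week 5, the one time that form is collected without a clinician-rated measure. The gap applies to all three arms and concerns at most 215 forms. How many would show a high caregiver score beside a low or missing adolescent item cannot be estimated from the document, and no rate is assumed.

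The conclusion rests on two assumptions: that the caregiver version includes the suicide item, which follows from its having the same questions, and that BASS is set up as section 9.4 is worded. If the flag is already active on the caregiver form, only the text needs correcting.

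This should not be read as saying that the trial lacks safety provision or that the self-guided arm goes unwatched. It has no bearing on sample size, power or error rates. The change is worth making because it is specific and nearly free, and it leaves the comparison of guided with self-guided treatment essentially untouched.

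**What to change.** In section 9.4, for all three arms, state that a score of 2 or 3 on the suicide item of the caregiver QIDS-A17-PR raises the same BASS flag and leads to the same telephone follow-up. Send the notice to team members who are not outcome assessors, so that masking is kept.

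The cost is one sentence, a configuration change and a few extra calls, some of which will be false alarms. No new measure is needed. The protocol is at version 1.5, dated October 2023, so for the week-5 form the change reaches only participants who have not yet passed that point. Its start date should be recorded.

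For lapsed adolescent forms, it is enough that the routines promised in section 6.4.1 list missing forms for review at the existing weekly conference. Automatic reminders, with a call after two consecutive missed forms, would be optional and are not needed for this point. The two-form threshold has no basis in the documents. Such a scheme would also need rules for the one- or two-week pauses allowed in guided treatment and for unanswered calls. It would add contact to the arm defined by having no therapist support, which touches the question in section 3 of whether that support matters.
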